## Annex 9: Sub study three Flow-diagram for educational intervention

**Arm 1**

Routine ANC & Newborn Services only

Absence of individualised prenatal health education; no CHW deployed; no mobile phones

**Primary outcomes**

1. Timely return visits
2. Completed Four ANC visits
3. Institutional Deliveries
4. Improved newborn care practices and newborn immunisation

**Outcomes**

Maternal mortality

Neonatal Mortality

**Arm 2**

Designated staff:

1. Health Assistant and
2. a team of 3 CHWs)

For educational intervention at the health facility

1. CHW using Mobile phones

Presence of individualised prenatal health education offered by CHWs; use of mobile phones to communicate vital information between CHWs and Health workers, provide reminders for return dates and delivery dates

## Annex 10: List of eligible Health Centres by HSD

| **S/N** | **HSD** | | |  |
| --- | --- | --- | --- | --- |
|  | **Buruli** | **Bujenje** | **Kibanda** |  |
| 1 | Kimengo | Budongo | Mutunda |  |
| 2 | Kilanyi | Ikoba | Diika |  |
| 3 | Pakanyi | Nyantonzi | Panyadoli |  |
| 4 | Nyakitibwa | Mihembero | Diima |  |
| 5 | Kyatiri | Ntooma | Karungi |  |
| 6 | Kigezi | Bwijanga | Kigumba |  |
| 7 | Kibwona | Kikingura | Katulikire |  |
| 8 | Kijunjubwa | Nyabyeya | Apodorwa |  |
| 9 | Kitanyaata | Kyamaiso | Mpuumwe |  |
| 10 | Kijenga | Kisalizi | Masindi port |  |
| 11 | Kibyamu |  |  |  |
| **Totals** | **11** | **10** | **10** | **31** |

| Annex 14: Budgetsi) Budget Sub study one: Assessing the primary health care workers' knowledge-base and perceptions about educational interventions during ANC clinics | | | | | | | | | | |
| --- | --- | --- | --- | --- | --- | --- | --- | --- | --- | --- |
| **Phase** | | **Activity Detail** | | **Number of Officers** | **Rate** | | **Number of days** | | **Totals** | |
| **Preparatory Phase** | | IRB costs | | 1 | 600,000 | | 1 | | 600,000 | |
|  |  | Uganda National Council of Science & Technology | | 1 | 720,000 | | 1 | | 720,000 | |
|  |  | Identify and Constitute Research Team Assistants etc | | 1 | 30,000 | | 1 | | 30,000 | |
|  |  | Per diems for Research Assistants | | 5 | 60,000 | | 10 | | 3,000,000 | |
|  |  | Per diems for Researcher | | 2 | 90,000 | | 10 | | 1,800,000 | |
|  |  | Training of Research Assistants | | 5 | 60,000 | | 3 | | 900,000 | |
|  |  | Pretesting of Study tools | | 1 | 100,000 | | 2 | | 200,000 | |
|  |  | Correction & Assembly of necessary study tools | | 200 | 300 | | 1 | | 60,000 | |
| **Field Costs** | | Local Car hire | | 2 | 80,000 | | 10 | | 1,600,000 | |
|  |  | Car Hired from Kampala | | 1 | 150,000 | | 12 | | 1,800,000 | |
|  |  | Fuel to and from Kampala | | 1 | 200,000 | | 2 | | 400,000 | |
|  |  | Fuel for Local field Travels | | 3 | 50,000 | | 10 | | 1,500,000 | |
| **Data Handling** | | Data entry & Cleaning | | 2 | 350,000 | | 7 | | 4,900,000 | |
|  |  | Data analysis | | 1 | 2,000,000 | | 1 | | 2,000,000 | |
|  |  | Manuscript writing | | 1 | 150,000 | | 1 | | 150,000 | |
| **Dissemination,**  **Manuscript writing and Publication** | | Discussions of results with District Officials | | 20 | 10,000 | | 2 | | 400,000 | |
|  |  | Discussion of results at the School of Public Health | | 1 | 100,000 | | 1 | | 100,000 | |
|  |  | Discussion of results at the MOH | | 20 | 50,000 | | 1 | | 1,000,000 | |
|  |  | Preparation of Manuscript for Publication | | 1 | 600,000 | | 2 | | 1,200,000 | |
|  | |  | |  |  | |  | | **22,360,000** | |
| Budget Sub study two: Determine prevalent prenatal and newborn homecare practices, their determinants and rationale | | | | | | | |  | |  |
| **Phase** | **Activity Detail** | | **Number of Officers** | | **Rate** | **Number of days** | | **Totals** | |  |
| **Preparatory Phase** | Uganda National Council of Science & Technology | | 1 | | 720,000 | 1 | | 720,000 | |  |
|  | IRB costs | | 1 | | 600,000 | 1 | | 600,000 | |  |
|  | Identify and Constitute Research Team Assistants etc | | 1 | | 30,000 | 1 | | 30,000 | |  |
|  | Per diems for Research Assistants | | 12 | | 60,000 | 10 | | 7,200,000 | |  |
|  | Per diems for Researchers | | 2 | | 90,000 | 10 | | 1,800,000 | |  |
|  | Training of Research Assistants | | 12 | | 60,000 | 4 | | 2,880,000 | |  |
|  | Pretesting of Study tools | | 1 | | 100,000 | 2 | | 200,000 | |  |
|  | Correction & Assembly of necessary study tools | | 200 | | 300 | 1 | | 60,000 | |  |
| **Field Costs** | Local Car hire | | 2 | | 80,000 | 10 | | 1,600,000 | |  |
|  | Car Hired from Kampala | | 1 | | 150,000 | 12 | | 1,800,000 | |  |
|  | Fuel to and from Kampala | | 1 | | 200,000 | 2 | | 400,000 | |  |
|  | Fuel for Local field Travels | | 3 | | 50,000 | 10 | | 1,500,000 | |  |
| **Data Handling** | Data entry & Cleaning | | 2 | | 350,000 | 7 | | 4,900,000 | |  |
|  | Data analysis | | 1 | | 2,000,000 | 1 | | 2,000,000 | |  |
|  | Manuscript writing | | 1 | | 150,000 | 1 | | 150,000 | |  |
| **Dissemination, Manuscript writing and Publication** | Discussions of results with District Officials | | 20 | | 10,000 | 2 | | 400,000 | |  |
|  | Discussion of results at the School of Public Health | | 1 | | 100,000 | 1 | | 100,000 | |  |
|  | Discussion of results at the MOH | | 20 | | 50,000 | 1 | | 1,000,000 | |  |
|  | Preparation of Manuscript for Publication | | 1 | | 600,000 | 2 | | 1,200,000 | |  |
| **TOTAL** |  | |  | |  |  | | **28,540,000** | |  |

| iii) Sub study three: Community trial: Intervention to enhance prenatal educational interventions by CHW at the primary healthcare level | | | | | |  |
| --- | --- | --- | --- | --- | --- | --- |
| **Phase** | **Activity Detail** | **Number of Officers** | **Rate** | **Number of days** | **Totals (Ug Shs)** | **Sub Totals** |
| **Preparatory Phase** | Uganda National Council of Science & Technology | 1 | 720,000 | 1 | 720,000 |  |
|  | Pre-visits to the district to discuss formative results with local team | 2 | 3,400,000 | 2 | 13,600,000 |  |
|  | Constitution of the local team | 2 | 250,000 | 2 | 1,000,000 |  |
|  | Presentation of study protocol to district officials | 25 | 12,000 | 2 | 600,000 |  |
|  | Discussions of terms of reference for local team | 80 | 12,000 | 4 | 3,840,000 |  |
|  | Roles and functions of team members | 80 | 12,000 | 2 | 1,920,000 |  |
|  | IRB costs | 1 | 600,000 | 1 | 600,000 |  |
|  | procurement of mobile cell phones | 36 | 100,000 | 1 | 3,600,000 |  |
|  | maintenance of mobile connectivity | 36 | 100,000 | 12 | 43,200,000 |  |
|  | Stationary costs for data files | 20 | 3,000 | 200 | 12,000,000 |  |
|  | Two-Monthly Field visits by PI | 1 | 3,500,000 | 6 | 21,000,000 |  |
|  | Correction & Assembly of necessary study tools | 200 | 300 | 1 | 60,000 | 102,140,000 |
|  |  |  |  |  |  |  |
| **Field Costs** | Local Car hire | 2 | 80,000 | 10 | 1,600,000 |  |
|  | Car Hired from Kampala | 10 | 150,000 | 5 | 7,500,000 |  |
|  | Fuel to and from Kampala | 10 | 200,000 | 2 | 4,000,000 |  |
|  | Fuel for field work | 12 | 50,000 | 5 | 3,000,000 |  |
|  | Monthly wages for CHWs | 22 | 10,000 | 12 | 2,640,000 |  |
|  | Compensation for HA supervising CHWs | 18 | 10,000 | 12 | 2,160,000 |  |
|  | Additional incentives for additional work done by Primary care facility staff | 22 | 5,000 | 12 | 1,320,000 |  |
|  | Transport refund for monthly review sessions with HA | 22 | 5,000 | 12 | 1,320,000 |  |
|  | Procurement of essential supplies and medicines at Primary care centres participating in the study | 15 | 100,000 | 12 | 18,000,000 |  |
|  | Monthly review of study progress | 20 | 12,000 | 12 | 2,880,000 |  |
|  | Fuel for Routine fort-nightly field visits by HA | 2 | 30,000 | 24 | 1,440,000 |  |
|  | Compensation of Health centre staff for additional work | 80 | 5,000 | 12 | 4,800,000 | 50,660,000 |
|  |  |  |  |  |  |  |
| **Assessment of Intervention** | Identify and Constitute Research Team Assistants etc | 1 | 30,000 | 1 | 30,000 |  |
|  | Per diems for Research Assistants | 12 | 60,000 | 10 | 7,200,000 |  |
|  | Per diems for Researchers | 2 | 90,000 | 10 | 1,800,000 |  |
|  | Training of Research Assistants | 12 | 60,000 | 4 | 2,880,000 |  |
|  | stationary for data collection and tools | 2 | 500,000 | 2 | 2,000,000 |  |
|  | Pretesting of Study tools | 1 | 100,000 | 2 | 200,000 | 14,110,000 |
|  |  |  |  |  |  |  |
| **Data Handling** | Data entry & Cleaning | 2 | 350,000 | 17 | 11,900,000 |  |
|  | Data analysis | 1 | 5,000,000 | 2 | 10,000,000 |  |
|  | Manuscript writing | 1 | 150,000 | 1 | 150,000 |  |
| **Dissemination and Manuscript writing and Publication** | Discussions of results with District Officials | 20 | 10,000 | 2 | 400,000 |  |
|  | Discussion of results at the School of Public Health | 1 | 100,000 | 1 | 100,000 |  |
|  | Discussion of results at the MOH | 20 | 50,000 | 1 | 1,000,000 |  |
|  | Preparation of Manuscript for Publication | 1 | 600,000 | 2 | 1,200,000 | 24,750,000 |
|  |  |  |  |  |  |  |
| **TOTAL** |  |  |  |  | **191,660,000** | **191,660,000** |

# Annex 15: SOPs: Standard Operating Procedure and intervention packages

### i) Standard operating procedure and intervention package for educational intervention during ANC

**(**[**Bhutta Z, Sajid S et al. 2011**](#_ENREF_10)**)**

When the pregnant women enter the clinic room

1. Identify pregnant women with all of the following conditions:
2. First visit of the current pregnancy,
3. Not more than 28 weeks of gestation
4. Administer the consent form
5. If she consents then open a file for her
6. Request for her ANC card
7. Enter all personal details available on the ANC card in to the file
8. Record any telephone contacts that you can use to access her in future

name, age, ethnicity, parity, LNMP, EDD, gestation age of the first visit, history of previous pregnancy outcome of the previous pregnancy (baby – alive or dead, mode of delivery), distance from the health facility, marital status, history of previous ANC attendance-Number of attendance, delivery (home, health facility, TBA etc).

Note the date for the next appointment, (all this information will be used to tailor the discussions)

-if she consistently attended all the expected milestones-then you find out what her motivation was to do so, and whether she plans to do the same for the current pregnancy;

- If not consistent-discuss the reasons for inconsistencies and help her to find a solution,

- diet during pregnancy-find out what foods are readily consumed and what she can easily afford, what foods could be prohibited during pregnancy (caution about antagonising cultures-you can find another acceptable alternative source of the food value) and discuss the importance for balances in diet, fruits, green vegetables, proteins and carbohydrates,

- Discuss work related activities-how much she does and who helps her with the routine household and garden chores.

- Discuss importance of ANC even when she has been attending consistently, the advantages of delivering in the health facility even when she has been delivering at the health facility,

- Birth preparation-clean clothes for the newborn (emphasis that clean does not mean new!-even old rages can be patched together washed clean, clean environment for the newborn,

- caring for the cord, dangers of applying substances to the cord,

- Pre-lacteal feeds-and its disadvantages-explain how breast milk eventually comes and the usefulness of colostrum.

- Discuss bathing of the new baby how soon and how to delay (delay up to 24 hours),

- Immunisation of the child, polio 0, BCG etc.

- Recognition of a sick child-hot to touch, refusing to feed, crying unusually,

All these information should be derived from discussions with the pregnant woman-not as a set of instructions to be strictly followed-compromises should be made at every stage-all that is agreed upon should be detailed down in the file. The counsellor should moderate the discussions, if the pregnant woman has come with a partner or a caretaker; both of them should be involved in the discussions even if the care taker is not pregnant-if there is a caretaker present then this should be recorded and state the relationship between them.

Tick the areas that were discussed, mark with a cross what you did not discuss with her, note down important decisions that you have agreed upon with the participant-you will use this as a reference point in subsequent meetings and discussions

Ensure that the discussion does not exceed 30 minutes unless there is expressed interest from the participant to continue. And this expression should be noted down in the file.

For subsequent visits indicate appointment dates and actual revisit dates

Later on follow-up for delivery and record where she has delivered from

Assess for the different practices outlined annex 6 will be used to assess the following outcomes

Place of delivery, Cutting of the cord, care for the cord, initiation of breast feeding, provision of pre-lacteal feeds, in case of illness how it was recognised, what action was taken, how soon was the care seeking from onset of disease or when the decision was made that the child was unwell, what facility did she take the child, outcome, at the periphery of assessment the researcher will want to know whether the child is still alive just at one month.

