# Operational definition of terms

*Primary healthcare facility* The first contact point for formal healthcare - In this case the first contact for which pregnant women access antenatal care i.e. health centres II, III, IV and ANC services at hospitals

*Prenatal service* -as prescribed by the WHO history taking, physical examinations, laboratory investigation, prescriptions, administration of folic acid and Ferrous tablet, assessment for referral, dialogue and discussions about pregnancy, dangers in pregnancy, hygiene, immunisations and birth preparedness

*Technical maternal and newborn services*-more clinical services for example history taking, physical examination like palpation, drawing of blood samples, estimating pelvic adequacy and assessing for referral

*Less technical maternal and newborn services*-services of a promotional nature health education, counselling, birth preparation which entails dialogue and discussions with the pregnant women and their attendants/caregivers

*Individual ANC educational interventions*- information given to a pregnant woman attending ANC based on the unique problems or demands or needs that she presents with during the current pregnancy as opposed to uniform information provided to all prenatal women

*Consistent ANC visits*-timely and completed four ANC visits

*Health worker with a promotional profile* a health worker with a formal employment in the district health system, whose primary training is health prevention and health promotion, does not routinely take part in clinical services like physical examinations, prescriptions of medicines or surgery – in this case we refer to the Health Assistant (HA)

*Homecare practices*-care provided to prenatal women and newborn babies at home based on knowledge and perception of the care givers (elements of care considered in this study are: nutritional care for pregnant women, care for the cord, warmth for newborn babies, and initiation of breastfeeding and neonatal immunisation status)

*Elderly caregivers*-these are usually women in the households, about 50 years or older. They provide neonatal care and advice to family members within the household sometimes extending to the immediate neighbours. As opposed to TBAs, they are not transactional. They provide expert opinion and demonstrate actual care to postnatal women within the household or immediate neighbourhood

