## 2.3 Delivery of the comprehensive ANC care model

Improving maternal and newborn survival by the delivery of an integrated comprehensive healthcare package through a continuum of care has been widely endorsed and advocated for ([WHO 2010](#_ENREF_113)). In this model a primary healthcare worker provides a series of both clinical and promotional interventions to a pregnant mother during ANC, through the intra-partum at delivery to the postnatal period.

Unfortunately, most pregnant mothers for varied reasons ([Waiswa P, Kemigisa M et al. 2008](#_ENREF_97)), attend the first antenatal visit and never return for subsequent visits, rarely completing the predetermined four visits for the entire gestation period. Moreover, many of them make the first visit late in to the second or third trimester ([WHO 2008a](#_ENREF_110)). This late attendance coupled with high attrition rates in ANC present a ‘missed opportunity’ for care-seeking mothers to receive a comprehensive package of preventive and promotional services.

Skilled attendance at birth although widely advocated for, amidst several health system challenges, has equally not gained any significance in sub Saharan Africa ([Waiswa P, Peterson S et al. 2010](#_ENREF_98))

A skilled attendant as defined by WHO is an accredited health professional, such as a midwife, a doctor or nurse ([WHO 2004](#_ENREF_114)). Inherent in this definition is the central role of the skilled attendant in the health system ([WHO 2004](#_ENREF_114)) acting as a link between the community and the tertiary level of care. During labour, only about 46% of the expected mothers get in to some contact with the formal healthcare system ([WHO 2009](#_ENREF_112)), a contact time that is usually inadequate to deliver all the important promotional and preventive health messages.

On the other hand, pregnant women and their newborn babies who never make any formal contacts with the healthcare system during the time of labour are faced with challenges related to practices and beliefs ([Choudhury and Ahmed 2011](#_ENREF_19)) such as early bathing of the baby, late initiation of breastfeeding, unhygienic practices ([Waiswa P, Kemigisa M et al. 2008](#_ENREF_97)) that are likely to jeopardise the health of both mother and the newborn. Moreover these risky practices are not just limited to the lower socio-economic class but have been shown to apply across all social classes ([Waiswa P, Peterson S et al. 2010](#_ENREF_98)).

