## 4.4.1 Introduction

The ultimate intervention will be based on data obtained from the two formative surveys and; based on our own knowledge about the context of Masindi and Kiryandongo and the subject of maternal and newborn care. The first study with health workers will inform the design of re-orienting health services at the antenatal clinic, while the community survey will form a basis for the appropriate educational messages to be delivered at the ANC clinics.

Primary outcomes of interest in this study are timely return ANC visits, completed four ANC visits, institutional delivery, and neonatal homecare practices. Secondary outcomes are post intervention community and health workers perceptions about the educational intervention offered by CHWs at the primary care facility.

The educational intervention will consist of **i)** a promotional team of community health workers supervised by a health assistant providing educational interventions at the primary care facility and; **ii)** the promotional team at the health centre using mobile phone reminders through Community Health Workers to pregnant women at the households.

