## Exclusion criteria:

i) Pregnant women above 28 weeks attending ANC in the 16 selected health centres of Masindi and Kiryandongo will be excluded

(ii) All pregnant women in Masindi and Kiryandongo who will not have enrolled for Antenatal Care visits in the targeted health centres by the time the two trail arms will be conducted.

(iii) Pregnant women in Masindi and Kiryandongo districts who would have enrolled for ANC in the selected health centres but found to be bed ridden or mentally disturbed.

All pregnant women recruited in to the study will be requested to provide two or three possible phone contacts through which they can be reached. These telephone contacts will be utilised during the follow-up stage in case the women do not make return visits. All health workers providing ANC care at the primary care facility will receive training in counselling. A standard operating procedure for the educational intervention at the ANC clinic to pregnant women will be developed (see annex 7.13), these messages will be adapted to suit the individual context and incorporate findings from formative surveys.

During ANC visits, qualified staff will first provide the more technical care to pregnant women and record all details on the patients card; this information will further be utilised by the team comprising of HA and CHWs to provide the targeted educational intervention; the promotional team will also engage the pregnant women to discuss in to details recommended aspects of care during pregnancy and newborn care like diet, birth preparation, danger signs in pregnancy, the advantages of delivering in the health facility and birth plans, care for the newborn including hygiene, breastfeeding care for the cord and warmth for the newborn.

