### 4.4.7 Study variables

## Independent/factor:

(i) Routine ANC care available in the health facilities (standard care);

(ii) *Promotional team* giving additional education care to pregnant women with periodic mobile phone reminders.

*Dependent/outcome variables*

1. Timely return ANC visits (return within seven days of the scheduled appointment date)
2. Completion of the four recommended ANC visits
3. Institutional deliveries
4. Newborn care practices:
5. Provision of warmth to the newborn
6. Initiation of breastfeeding within one hour of birth
7. Care for the cord
8. Immunization for the newborn-Polio 0 & 1; BCG within the neonatal period

We will, at the end of the study, assess perceptions of individual women who have participated in this intervention towards the integrated package by administering the tool described by Howie and others ([Howie J, Heaney D et al. 1998](#_ENREF_42)) elaborated in annex 15 (the Patient-Enablement Initiative (PEI).

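### The draft counselling list in Annex 15 i) has no item on danger signs in pregnancy and never says when to start breastfeeding

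*Protocol*

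**What the plan says.** Section 4.4.6 (the intervention text below the exclusion criteria) lists what the promotional team will discuss with each woman. The list includes "danger signs in pregnancy, the advantages of delivering in the health facility and birth plans, care for the newborn including hygiene, breastfeeding", and goes on to cord care and warmth. The same section says that an operating procedure will be developed and that "these messages will be adapted to suit the individual context and incorporate findings from formative surveys".

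Annex 15 i) is the only counselling procedure shown. It sets out the discussion topics as dashed lines and then instructs: "Tick the areas that were discussed, mark with a cross what you did not discuss with her". It also says that the content should come out of discussion and need not be followed rigidly, and it sets a 30-minute limit that may be exceeded if the woman wishes.

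On outcomes, section 4.4.1 states: "Primary outcomes of interest in this study are timely return ANC visits, completed four ANC visits, institutional delivery, and neonatal homecare practices". Section 4.4.7 lists four newborn care practices, one of which is "Initiation of breastfeeding within one hour of birth". Annex 15 i) closes with the practices to be assessed after delivery, start of breastfeeding among them, and names Annex 6 as the tool.

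On the source of the messages, section 4.4.1 says that "the community survey will form a basis for the appropriate educational messages to be delivered at the ANC clinics".

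**The concern.** The list is what community health workers would have in front of them, and what they would tick or cross. A topic that is not on it is neither prompted nor reliably recorded. Two topics that the protocol treats as important are absent.

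For danger signs in pregnancy, the stake is fidelity to the promised intervention and the safety content of the counselling. For the timing of the first breastfeed, it is interpretation. The trial counts this practice within a primary outcome, but the drafted procedure does not ask the counsellor to raise its timing. If the list were used unchanged and no difference appeared on this practice, the practice might be unresponsive to education by community health workers, or its timing might not have been raised.

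**Working it through.** No sample-size or power figure is involved. The check sets the texts side by side.

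**Step 1: the discussion lines in Annex 15 i).** There are 11: (1) past consistent attendance; (2) reasons for past inconsistency; (3) diet; (4) workload; (5) value of ANC and of facility delivery; (6) birth preparation; (7) cord care; (8) pre-lacteal feeds and colostrum; (9) delaying the bath; (10) immunisation; (11) recognising a sick child.

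**Step 2: compare with the promise and the outcome.**

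| Topic | Where it is promised or measured | Lines in Annex 15 i) |
|---|---|---|
| Danger signs in pregnancy | Section 4.4.6, topics to be discussed | 0 of 11; line 11 concerns the child only |
| Time of first breastfeed | Section 4.4.7, component of a primary outcome; assessed after delivery under Annex 15 i) | 0 of 11; line 8 is related but gives no timing |

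**Step 3: does the rest of the protocol treat these topics as incidental?** It does not. Section 3.1 builds its case on fewer than 50% of ANC attenders in sub-Saharan Africa being told about danger signs, birth preparation or the importance of facility delivery. Annex 15 i) has lines for the second and third and none for the first. Section 2.3 names risky practices "such as early bathing of the baby, late initiation of breastfeeding, unhygienic practices"; the list deals with the bath, and gives a time for it, but not with late breastfeeding.

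**Step 4: would the planned adaptation supply the items?** Not necessarily.

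- *Danger signs.* The maternal variables of the community survey (section 4.3.7) are nutrition, start of ANC, birth preparation and exertion. Danger signs in pregnancy are not among them. Sub-study one covers them, but as health-worker knowledge (section 4.2.8, Annex 1).
- *Start of breastfeeding.* Section 4.3.7 names it as a survey variable, but none of sections A to H of the Annex 6 questionnaire asks when breastfeeding began. The community-side question on first feeding is in the interview guide for elderly caregivers and birth attendants (Annex 7). Annex 1 asks health workers when breastfeeding should start, which is again knowledge and not practice.

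**Step 5: can the outcome be read from the named tool?** Annex 15 i) points to Annex 6 for the post-delivery assessment. As Annex 6 has no question on when breastfeeding began, it cannot show whether a woman started within the hour. Adding the message alone would therefore not make this component interpretable; the question is needed too.

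**The case against.** The strongest reply is that nothing has been fixed. Section 4.4.6 says the messages will be adapted, and section 4.4.1 says the final intervention will rest on the formative data. The list itself is a flexible guide, and the governing text already commits the team to danger signs and breastfeeding. Section 1.5.3 adds emergency conditions and responses to the information to be given. This stands, and it limits the weight of the point: a reader might infer that the protocol drops danger signs from the intervention, and the documents do not support that. But flexibility governs how listed topics are discussed. Neither it nor the promise to adapt puts the two absent prompts on the list.

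A second reply is that section 4.4.6 promises breastfeeding without any timing, and that advice against pre-lacteal feeds and in favour of colostrum bears on early feeding. This also stands. The breastfeeding gap is therefore no contradiction of section 4.4.6; it is a gap between the list and the outcome in section 4.4.7.

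Third, a reader might infer that a fixed share of the newborn outcome has no matching message. The documents give no consistent count. Warmth is reached only indirectly, through the bath and clothing lines. If indirect coverage counts, breastfeeding is arguably covered too; if it does not, warmth is also missing.

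Fourth, the front-matter definition of prenatal service, which includes "dialogue and discussions about pregnancy, dangers in pregnancy, hygiene, immunisations and birth preparedness", describes WHO-prescribed care in general and not the community health workers' package. It shows the topic is recognised and adds little more. The phone procedure in Annex 15 ii) also provides for enquiries about pregnancy, closer follow-up of complications and emergency evacuation. Women would thus not be without cover, although none of this teaches them the signs.

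**Conclusion.** The point holds as a minor alignment. Of the 11 discussion lines, none raises danger signs in pregnancy, which section 4.4.6 says will be discussed, and none says when to start breastfeeding, which section 4.4.7 measures. Only one practice within one of the four primary outcomes is touched. Sample size, power and the institutional-delivery comparison are unaffected. Danger-sign knowledge is not an outcome, so that omission affects no comparison between arms.

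A reader might go further and conclude that a null result on early breastfeeding would be ambiguous solely because of the missing message. That presumes the timing is measured, and the Annex 6 questionnaire does not ask it.

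The conclusion rests on two assumptions: that adaptation would leave the list as drafted on these two topics, and that Annex 6 is used for the outcome as Annex 15 i) says. Section 4.4.9 mentions semi-structured questionnaires for the trial without identifying them. If one of those asks when breastfeeding began, the measurement half falls away and the two missing prompts remain.

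**What to change.** When Annex 15 i) is adapted before enrolment, add two discussion-and-tick items: danger signs in pregnancy, and a first breastfeed within one hour of birth. If the soft 30-minute limit binds, spread the topics over return visits.

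Add one question to Annex 6 on how soon after birth the baby was first breastfed, with a response category that separates the first hour. It should be in place before Annex 6 is used for trial outcomes, whether or not the community survey has already been done.

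The cost is two lines in a draft procedure and one questionnaire item. Design, sample size and analysis do not change.
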